# Effectiveness of a Walking Program Involving the Hybrid Assistive Limb Robotic Exoskeleton Suit for Improving Walking Ability in Stroke Patients: Protocol for a Randomized Controlled Trial

**DOI:** 10.2196/14001

**Published:** 2019-10-11

**Keywords:** Hybrid Assistive Limb (HAL), gait training, stroke, hemiparesis

## Abstract

**Background:**

Gait disturbance often occurs in stroke survivors. Recovery of walking function is challenging, as some gait disturbance due to hemiparesis often remains even after rehabilitation therapy, presenting a major obstacle towards regaining activities-of-daily-living performance and achieving social reintegration.

**Objective:**

This study aims to clarify the effectiveness of a walking program involving the wearable Hybrid Assistive Limb (HAL-TS01) robotic exoskeleton for improving walking ability in stroke patients with hemiparesis and stagnant recovery despite ongoing rehabilitation.

**Methods:**

This is a multicenter, randomized, parallel-group, controlled study (HAL group, n=27; control group, n=27). The study period includes preintervention observation (until stagnant recovery), intervention (HAL-based walking therapy or conventional rehabilitation; 5 weeks), and postintervention observation (2 weeks). Following provision of informed consent and primary registration, the patients undergo conventional rehabilitation for preintervention observation, during which the recovery of walking ability is monitored to identify patients with stagnant recovery (based on weekly assessments using the 10-meter maximum walking speed [MWS] test). Patients with an MWS of 30-60 m/minute and insufficient weekly improvement in MWS undergo secondary registration and are randomly assigned to undergo HAL-based walking therapy (HAL group) or conventional rehabilitation (control group). The primary outcome is the change in MWS from baseline to the end of the 5-week intervention.

**Results:**

This study began in November 2016 and is being conducted at 15 participating facilities in Japan.

**Conclusions:**

Assessments of walking ability vary greatly and it is difficult to define the threshold for significant differences. To reduce such variability, our study involves conducting conventional rehabilitation to the point of saturation before starting the intervention. Stagnation in the recovery of walking ability despite conventional rehabilitation highlights the limits of current medical care. The present study may bring evidence that HAL-based therapy can overcome such limitations and induce added recovery of walking ability, which would promote the use of HAL technology in the clinical setting.

**Trial Registration:**

UMIN Clinical Trials Registry UMIN000024805; https://upload.umin.ac.jp/cgi-open-bin/ctr_e/ctr_view.cgi?recptno=R000028545

## Introduction

At stroke onset, more than 60% of patients have gait disturbance and about 50% are unable to walk [1,2]. Recovery of walking function is generally a long and arduous process [1,3,4]. Current rehabilitation strategies for poststroke gait disturbance are quite effective, but patients with severe gait disturbance may not fully recover their walking ability. Furthermore, such gait disturbance is a major obstacle towards recovering activities-of -daily-living (ADL) performance and achieving social reintegration.

The Hybrid Assistive Limb (HAL) manufactured by Cyberdyne Inc. (Tsukuba, Japan) is a robotic exoskeleton that aids body movements by detecting and enhancing bioelectric signals to the muscles. When a person tries to move a muscle, a signal is transmitted from the brain through the spinal cord and motor neurons to said muscle, causing the musculoskeletal system to move. This process is accompanied by weak bioelectric signals detectable at the surface of the skin. The HAL was developed to read such bioelectric signals and help with movement per the person’s intentions [5,6]. Different hypotheses have been proposed about the effects of HAL therapy, including the interactive bio-feedback hypothesis and neural plasticity [7], but these remain unproven. Clinical studies conducted in Japan confirmed the clinical effects of HAL therapy and, in November 2015, a leg-type bipedal HAL was approved as a new medical device for managing spinal muscular atrophy, spinal and bulbar muscular atrophy, amyotrophic lateral sclerosis, Charcot-Marie-Tooth disease, distal myopathy, inclusion body myositis, congenital myopathy, and muscular dystrophy, apart from this clinical trial.

Whereas the mechanisms underlying the therapeutic action of the HAL have not been completely clarified, some researchers believed that HAL therapy is superior to standard robot-assisted training because it supplies better feedback and supports natural motions. Several earlier studies have examined the effectiveness of HAL-based walking exercises for alleviating gait disturbance in stroke patients. In a study on the stages of recovery after stroke, Kawamoto et al [8] showed that 16 sessions of HAL-based walking exercise increased walking speed and improved balance ability. In a randomized pilot trial, Watanabe et al [9] also found that 12 sessions of HAL-based walking exercise were more effective than conventional walking rehabilitation in terms of improving the functional ambulation category. Thus, these papers have confirmed the feasibility of HAL for clinical application.

Unlike prior studies, the present trial is designed to examine the effectiveness of HAL-based walking exercise in stroke patients with stagnant recovery under conventional rehabilitation. This is necessary because there is considerable variability on how recovery is assessed and what constitutes a meaningful rate of improvement. Therefore, the present study includes a preintervention observation period during which conventional rehabilitation for walking ability is performed until stagnation of recovery is noted. The fact that some patients no longer experience an improvement in walking ability despite continuing rehabilitation therapy highlights the current limits of conventional rehabilitation programs. The present study may bring evidence that HAL-based intervention can induce added recovery of walking ability in such patients, which would promote the use of HAL-based walking therapy in the clinical setting.

## Methods

### Study Objectives

The present study aims to clarify the efficacy of a HAL-based walking program versus conventional rehabilitation focused on restoring walking ability in patients with hemiparesis due to stroke.

### Study Design

The present study is designed as a multicenter, randomized, parallel-group, controlled trial. Our aim is to enroll 54 participants (27 in the HAL group and 27 in the control group) by December 2019. The patients have been recruited since November 2016, and the intervention is being conducted at 15 participating facilities.

The study has three phases (preintervention observation, intervention, and postintervention observation, as seen in Figure 1). Because of the evaluation of treatments that improve walking ability, this clinical trial focuses on walking ability rather than the severity of stroke to evaluate the patients.

The primary outcome of the study is the change in maximum walking speed (MWS) on the 10-m walk test from baseline to the end of the 5-week intervention. However, patients’ ADL or social reintegration are the true outcome, with walking ability selected as the surrogate outcome that was strongly associated with ADL or social reintegration [10]. In order to clarify whether the HAL-based walking program can boost walking ability once recovery has become stagnant despite ongoing conventional rehabilitation, the intervention is indicated only for patients who exhibit stagnant recovery of MWS, which is defined as insufficient weekly improvement in the MWS during the preintervention observation period. In addition to MWS, walking ability is also evaluated based on a patient’s ability to walk independently, but in this clinical trial the patients were only assessed with MWS because of its quantitative nature. The MWS values are measured every week and then smoothed over the current and previous two weeks (Standalone Equation 1) (Figure 2). The weekly rate of change in the smoothed MWS is obtained to determine the recovery rate (Standalone Equation 2). Stagnant recovery of MWS is then defined as <10% improvement compared to the previous week. Patients with an MWS of 30-60 m/minute and stagnant recovery of MWS are randomly assigned to either the control group or the HAL group.

**Figure 1 figure1:**
[figure not shown]
Study design. This multicenter, randomized, parallel-group, controlled study has three phases (preintervention observation, intervention, and postintervention observation). Following primary registration, the patients undergo conventional rehabilitation and are monitored to detect stagnant recovery. Upon secondary registration prior to the intervention, the patients are randomized to undergo conventional rehabilitation aimed at regaining walking ability (control group), or a walking program involving the use of the Hybrid Assistive Limb (HAL) robotic exoskeleton (HAL group).

**Figure 2 figure2:**
[figure not shown]
Method for smoothing the value of the maximum walking speed on the weekly 10-m walk test. MWS: maximum walking speed. (Xⅰ): MWS value measured for week i. (dⅰ): Smoothed MWS value for week i, obtained as a moving average of the MWS values measured for weeks i, i-1, and i-2.

This protocol has been approved by the Central Institutional Review Board of the Ibaraki Clinical Trial & Research Network. The research leader has notified the regulatory authorities with respect to the design and schedule of the clinical trial and has registered the study with the University Hospital Medical Information Network (UMIN trial registration number: UMIN000024805) prior to starting patient registration. Candidate patients are enrolled only upon supplying written informed consent for participation.

### Registration and Randomization

Upon supplying written informed consent, the patients were evaluated for eligibility according to the inclusion and exclusion criteria for primary registration. Registered patients who had completed the preintervention observation were evaluated for eligibility according to the inclusion and exclusion criteria for secondary registration. Stratified randomization was conducted, with MWS at allocation (<45 or ≥45 m/minute), age at the time of consent (<60 or ≥60 years), and the intervention center as the stratification factors. Data program and randomization program were served by CIMIC Co., Ltd. (Tokyo, Japan).

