### Sample Size

The main purpose of this study is to confirm the superiority of the HAL-based walking exercise (HAL group) over conventional rehabilitation focused on improving walking ability (control group), and the main outcome is MWS improvement. Based on a previous clinical study [10] that compared a HAL group and a non-HAL group, and taking into consideration the fact that this is a multicenter study, the clinically meaningful between-group differences in mean MWS and associated standard deviation were conservatively estimated at 9 m/minute and 11 m/minute, respectively. A minimum sample size of 50 participants (25 patients per group) is expected to provide a power of 0.8 for detecting such differences, with two-sided significance of 0.05. Assuming a dropout rate of around 5%, we aim to include 54 participants (27 per group).

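### Stratifying 54 patients by 15 centres, two MWS groups and two age groups makes 60 cells; if blocks are run within those cells, balance is weakened, though not lost

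*Protocol article*

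**What the plan says.** Registration and Randomization in the protocol article fixes the three factors and their levels: "Stratified randomization was conducted, with MWS at allocation (<45 or ≥45 m/minute), age at the time of consent". Age is split at 60, and the treating centre is the third factor. The section adds that an outside company supplied the randomisation program. It gives no block size and does not say whether the factors are crossed or balanced on their margins.

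Study Design gives the size of the trial: "Our aim is to enroll 54 participants (27 in the HAL group and 27 in the control group) by December 2019". The same section gives the number of centres: "the intervention is being conducted at 15 participating facilities".

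Statistical Analysis lists the terms of the primary repeated-measures model as group, period, their interaction, baseline MWS and age. Centre is not among them.

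**The concern.** Blocked randomisation within strata balances the arms only where blocks fill. With more strata than patients, most strata receive no patient or one, and the single patient's assignment is a coin toss that nothing in the stratum offsets. The balance on MWS and age that four strata would secure is then diluted by the addition of a 15-level factor.

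The stake is modest but real. The trial is small, and patients and investigators cannot be blinded after allocation. MWS at entry is also the baseline of the primary outcome. A visible imbalance in arm sizes or in entry MWS would invite doubt about the comparison and cost a little precision. Moreover, the factor that makes the cells sparse is the one factor of the three that the stated primary model leaves out.

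**Working it through.** **1. The plan's own figure.** Inputs from Sample Size: a between-group difference of 9 and an SD of 11 m/minute, a two-sided 5% level and dropout of about 5%. The stated result is: "A minimum sample size of 50 participants (25 patients per group) is expected to provide a power of 0.8". The exact two-sample t test has power 0.792 at 24 per arm and 0.809 at 25 per arm, so 25 per arm is right. 25 / 0.95 = 26.3, rounded up to 27 per arm, 54 in all. The sample size reproduces and this point does not affect it.

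**2. Number of cells.** 15 centres x 2 MWS x 2 age = 60; 54 / 60 = 0.9 patients per cell.

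**3. How sparse the cells are.** With 60 equally likely cells:
- expected empty cells: 60 x (59/60)^54 = 24.2
- expected single-patient cells: 54 x (59/60)^53 = 22.2

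Real cells are unequal. In simulation with unequal cells, about 28–34 cells are occupied and about 16–20 of these hold a single patient. More than half of the occupied cells therefore cannot complete even a block of 2.

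**4. Effect on balance.** 4,000 simulated trials of 54 patients per setting. Assumptions not in the document: 50/50 split on MWS, 30/70 split on age, centres recruiting equally or in proportion to 1/rank, and the block sizes shown. Ranges run over the two centre patterns. The gaps are the mean absolute difference between arms in the percentage of patients in the upper MWS group or the younger age group.

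| Scheme | Mean arm difference | Difference ≥6 | Exactly 27:27 | MWS gap (points) | Age gap (points) |
|---|---|---|---|---|---|
| Simple randomisation | 5.9 | 50–51% | 11% | 11 | 10 |
| 60 cells, blocks of 2 | 3.5–3.9 | 27–31% | 15–19% | 6.7–7.3 | 6.5–7.2 |
| 60 cells, blocks of 4 | 4.2–4.9 | 35–41% | 12–15% | 8.0–9.1 | 7.8–8.7 |
| 60 cells, blocks of 6 | 4.6–5.2 | 38–45% | 12–14% | 8.6–10.2 | 8.5–9.3 |
| MWS x age only, blocks of 4 | 1.3 | 0.3% | 43–44% | 2.5 | 2.9 |
| Minimisation on three factors (probability 0.8) | 1.2 | 0.5–1.0% | 47% | 3.5–3.6 | 3.8 |

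Repeat runs move these figures by a point or two; for blocks of 2 or 4 the chance of a difference of 6 or more is about 26–41%.

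**5. Effect on power.** Exact t test, difference 9, SD 11. With all 54 analysed: 0.839 at 27:27, 0.835 at 24:30, 0.826 at 22:32, 0.813 at 20:34. With 5% dropout (54 x 0.95 = 51 analysed): 0.817 at 26:25; 0.810 at 22:29 (from 23:31); 0.799 at 20:31 (from 21:33). A split of 21:33 or worse occurs in about 1–7% of trials with blocks of 2 or 4.

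**6. Cost of centre in the model.** The variance of the group effect is proportional to 1 / RSS, where RSS is the residual sum of squares from regressing the group indicator on the other model terms. In the same simulations, adding 14 centre indicators to the MWS and age groups raises this factor by about 21–22% under minimisation and 32–39% under MWS x age strata, before any reduction in residual variance. That is too much for about 54 / 15 = 3.6 patients per centre.

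**The case against.** The strongest reply is that the premise is not in the article. It names factors, not permuted blocks, block size or crossed cells. A central program that balances the same factors dynamically would fit the wording, and the sparse cells would then not matter. A journal article may leave the algorithm to the full protocol. This stands, and it is why the point is conditional. It does not remove the point, because separate lists within crossed strata is the ordinary meaning of stratified randomisation and the text does not mention minimisation.

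A reader might go further and infer that the scheme cannot deliver 27 per arm, or that it amounts to simple randomisation. The documents do not support either. The 27 per arm is stated as an aim, and an exact split still occurs in 12–19% of simulated trials with within-cell blocks. The mean arm difference of 3.5–5.2 is below the 5.9 of simple randomisation.

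Two further replies also stand. Chance imbalance after valid randomisation does not bias the comparison, and the primary model already adjusts for baseline MWS and age. The time left for a change is also short: the article is dated October 2019 and enrolment was due to end in December 2019.

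**Conclusion.** The concern holds as a conditional design point of small size. The 60 cells for 54 patients follow directly from the article. If blocks are run within those cells, a difference of 6 or more patients between arms occurs in about 26–41% of trials (blocks of 2 or 4), against about 1% or less under either alternative, and the mean gap between arms on the MWS stratum is roughly two to three times as large.

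Nothing here threatens validity or type I error, and power stays at or above about 0.80 for all but rare splits. The case rests on balance and credibility in a small open-label trial.

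The size depends on assumed MWS and age splits, centre recruitment patterns and block sizes, none of which the article gives. If the central program already balances on margins, one sentence saying so closes the point.

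**What to change.** First, state the allocation algorithm. Unless it already balances on margins, then for patients still to be allocated either:

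- use minimisation with a random element on the same three factors, or
- stratify on MWS and age only.

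In either case, include centre in the primary model as a random effect, not as 14 fixed-effect terms.

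If allocation is essentially complete, keep the algorithm, report balance for each of the three factors, and add the random centre effect.

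Cost: a change in the central allocation program and an amendment; no extra patients. The change helps only patients not yet allocated, and the switch of algorithm must be documented and reported. The MWS x age option gives up balance within centres, which has some value here because HAL operators and assessors are organised by facility; minimisation keeps centre among the balanced factors.

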### Inclusion and Exclusion Criteria

Two sets of inclusion and exclusion criteria were employed in this study, namely at the time of primary and secondary registration. The inclusion criteria for primary registration included: (1) hemiparesis due to stroke; (2) age ≥18 years; (3) ≤5 months from stroke onset; and (4) ability to give written informed consent. Furthermore, patients had to be able to come in for inpatient evaluations during the study period and had to be able to wear and use the HAL robotic exoskeleton. Patients with subarachnoid hemorrhage, which involves bleeding in the subarachnoid space and is thus distinct from brain hemorrhage or cerebral ischemia, were excluded. Patients who achieved enough improvement in walking ability and become able to walk outdoors unassisted were also excluded, as they might not have benefitted as much from HAL therapy. For safety reasons and due to the specific nature of the device and training program, patients with any of the following conditions were also excluded: (1) severe akinesia, rigidity, or schizophrenia; (2) difficulty performing rehabilitation in the training room; (3) a condition other than the culprit cerebrovascular disease that makes it difficult for the patient to understand instructions; (4) impaired walking function due to a disease of the spinal cord, peripheral nerves, or skeletal muscles, or due to trauma, severe impairment of deep sensibility, or severe lower limb ischemia; or (5) other severe uncontrollable diseases.

The inclusion criteria for secondary registration were: (1) insufficient rate of weekly improvement in MWS (smoothed value) during preintervention observation (<10% improvement relative to the previous week); and (2) MWS of 30-60 m/minute at the final measurement during preintervention observation. Among patients who are able to wear the HAL robotic suit, we excluded those unable to operate it in the Cybernic Voluntary Control mode with both hips and knees, in which it can assist with movement in accordance with the person’s intentions.

### Discontinuation From the Study

Investigators and other persons involved are permitted to discontinue the study if consent is withdrawn, if it is discovered that an exclusion criteria is satisfied, if an adverse event or another circumstance renders the patient unable to participate in the intervention for ≥1 week at a time, or if it is deemed difficult to continue the study and valid to discontinue it for efficacy or safety reasons.

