### Statistical Analysis

The efficacy of HAL-based therapy will be analyzed using the full set of data based on the intention-to-treat principle, and using the per-protocol set. The change in MWS from baseline (right before intervention) to week 5 of the intervention, which is the primary outcome, will be compared between the HAL group and the control group using a mixed model, repeated-measures analysis that includes group and intervention period (weeks 1-5) as factors, and group × period interaction, baseline MWS, and age as covariates. The change in mean step length and the change in average step rate at MWS will be similarly analyzed. Other secondary endpoints at 5 weeks will be analyzed using analysis of covariance, which will include group as a factor, and relevant baseline values and age as covariates. The number and percentage of patients who develop adverse events will be summarized for each group and compared between the two groups using Fisher’s exact test. The level of significance is set at 0.05 for all analyses.

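### The discontinuation rule ends study participation, not only the intervention, on adherence and efficacy grounds, so the intention-to-treat comparison is not protected from informative loss of data

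*Protocol article*

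**What the plan says.** The rule stands in the protocol article under the heading "Discontinuation From the Study". It begins: "Investigators and other persons involved are permitted to discontinue the study if consent is withdrawn, if it is discovered that an exclusion criteria is satisfied". Two further grounds follow in the same sentence. One is an adverse event or other circumstance that "renders the patient unable to participate in the intervention for ≥1 week at a time". The other applies "if it is deemed difficult to continue the study and valid to discontinue it for efficacy or safety reasons". No criterion for efficacy is given, nor whether lack of benefit or sufficient benefit is meant. The section has no separate category for a patient who stops the intervention but remains in follow-up.

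The Statistical Analysis section says that efficacy will be "analyzed using the full set of data based on the intention-to-treat principle, and using the per-protocol set". The primary outcome, change in maximum walking speed (MWS) from baseline to week 5, is compared by a repeated-measures mixed model over weeks 1 to 5. Step length and step rate are treated in the same way. The other secondary endpoints are compared at week 5 by analysis of covariance. The Sample Size section allows for about 5% dropout. The limitations in the Discussion state that patients and investigators cannot be blinded after allocation.

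**The concern.** An intention-to-treat comparison needs the outcome of every randomised patient whatever happens to treatment. Apart from withdrawal of consent, the grounds listed pull the other way. Missing a week or more of intervention is non-adherence, and the principle exists to keep such patients in the comparison. An eligibility breach found after randomisation is not normally a reason to lose the outcome. An efficacy ground can tie the loss directly to the primary outcome. Each decision is discretionary and is made by someone who knows the arm. Separate groups of physical therapists operate the device and assess patients, but that protects the measurement of MWS, not the decision about who is still measured.

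At stake is whether the patients contributing week-5 data in the two arms remain comparable. An analysis plan cannot recover walk tests that were never done.

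**Working it through.** **1. The plan's own figure.** Inputs from Sample Size: difference 9 m/minute, SD 11 m/minute, two-sided 0.05, power 0.8.
- Normal approximation: n per group = 2 × (1.960 + 0.842)² × 11² / 9² = 23.45, so 24.
- Two-sample t-test: 24.45, so 25, with power 0.809.
- Dropout: 25 / 0.95 = 26.3, so 27 per group and 54 in total.

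The stated 25 and 27 per group reproduce. The allowance is 0.05 × 54 = 2.7 patients. With losses spread evenly, a t-test on the remaining patients has power 0.819 at 5% loss, 0.798 at 10% and 0.747 at 20%.

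**2. The two sections side by side.**

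| Ground for leaving the study | What the intention-to-treat analysis needs |
|---|---|
| Consent withdrawn | Loss may be unavoidable |
| Exclusion criterion discovered | Patient kept as randomised |
| Intervention missed for a week or more | Patient kept; this is non-adherence |
| Continuing judged difficult and stopping valid for efficacy or safety | Outcome kept, or loss may depend on outcome |

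**3. How far the mixed model helps.** The article gives no discontinuation rate, so this is an illustration. Assumed: 27 per arm; weekly change follows a random walk with week-5 SD 11; control gain 3 m/minute; a likelihood-type estimator, valid under missing at random, stands in for the mixed model; 1,500 replicates. The Monte Carlo standard error is about 11 × √(2/27) / √1500 = 0.08 m/minute. In pattern A, HAL patients leave once their change falls below −8 m/minute; in pattern B, below −12. Placing the loss in one arm is a device of the illustration, not a claim about this trial.

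| Pattern | Triggering value | True difference | Model estimate | Completers only | HAL-arm loss |
|---|---|---|---|---|---|
| A | recorded | 0 | −0.02 | 3.29 | 21% |
| A | recorded | 9 | 8.99 | 10.30 | 8% |
| A | not recorded | 0 | 2.21 | 4.06 | 25% |
| A | not recorded | 9 | 9.62 | 10.48 | 9% |
| B | recorded | 0 | 0.07 | 1.83 | 10% |
| B | not recorded | 0 | 1.15 | 2.44 | 13% |

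With the triggering value on file, the model is close to unbiased. Without it, the error under no true effect is 1.15 to 2.21 m/minute, which is 1.15/9 = 13% to 2.21/9 = 25% of the planned difference. The discontinuation section does not require a final measurement, and a patient absent for a week may have none.

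**4. Week-5 endpoints.** Single-leg support time, 6-minute distance, functional ambulation category, Berg Balance Scale and Fugl-Meyer leg score are compared at week 5 by analysis of covariance. A patient without a week-5 value does not contribute. The completers-only column shows the mechanism on the MWS scale: distortion remains even when the triggering MWS was recorded.

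**5. What the illustration leaves out.** It assumes that a patient's course after leaving is what it would have been on continuing. If the course changes once the intervention stops, a missing-at-random model describes continued treatment, not the effect of assignment.

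**The case against.** The strongest reply is that this is a condensed article. It says that investigators may discontinue, not that they must. No sentence says that MWS measurement stops or that such patients leave the full set, and the assessment schedule is in an appendix that is not shown. The efficacy ground has a second condition, that continuing is judged difficult. The planned model uses all values recorded before exit and, as shown above, can be nearly unbiased.

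Most of this stands, and it limits the point. It does not remove it, because the article states the level of the rule (the study) and its grounds, and these fit badly with the analysis it promises. With unblinded investigators, discretion adds to the difficulty.

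Three stronger readings are not supported:
- **Responders are removed.** A reader might combine the rule with the criterion "Patients who achieved enough improvement in walking ability and become able to walk outdoors unassisted were also excluded". But the article applies its criteria at primary and secondary registration, before the intervention, and does not say that this one is reapplied during weeks 1 to 5.
- **Loss is greater in the HAL arm.** The article gives no rates by arm. It says only that device malfunctions are recorded, and it requires patients to be able to wear and operate the device.
- **Naming two analysis sets inflates type I error.** Nothing says that success in either set would count, and ranking the sets is commonly left to the statistical analysis plan.

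**Conclusion.** The point holds as a mismatch between two stated parts of the protocol article. Discontinuation is defined at study level on grounds related to adherence and possibly to outcome, by unblinded investigators, while the efficacy analysis rests on the intention-to-treat principle. A reader might conclude that this comparison cannot be made. That goes too far: the rule is permissive, and the mixed model limits bias in the primary outcome when the values that prompted discontinuation were recorded. The comparison is better described as unprotected.

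The size and direction of any bias are unknown. The 1.15 to 2.21 m/minute found under no true effect rests on assumed discontinuation patterns with 13% to 25% loss in one arm, well above the 5% planned for, and on an unrecorded triggering value. The week-5 covariance endpoints are more exposed. The change is justified because it is cheap and data not collected during the trial cannot be recovered, not because a bias has been demonstrated.

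**What to change.** Reconcile the discontinuation section with the Statistical Analysis section. State that, after randomisation:
- stopping the intervention, or discovering an exclusion criterion, does not end follow-up;
- every randomised patient who has not withdrawn consent to follow-up keeps the scheduled MWS tests to week 5 and the week-5 secondary assessments, where feasible and safe;
- these patients are analysed as randomised in the full set.

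The rules for stopping treatment itself are not touched. If the full protocol already says this, the article's wording only needs to be aligned with it.

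The cost is one amended paragraph and a few already scheduled assessments in patients who are off the intervention. The effect estimate may be slightly diluted, because it then includes patients who did not complete the program.
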